#### Relevant concomitant care permitted or prohibited during the trial {11d}

Individuals who are currently receiving psychotherapy cannot participate in the trial.

#### Provisions for post-trial care {30}

n/a, explanation: There is no anticipated harm and compensation for trial participation. Since there are no established interventions recommended for the target population of this trial, there will be no ancillary and post-trial care.

### Outcomes {12}

Outcomes will be assessed at three measurement timepoints: pre-intervention (i.e., pre-randomization), post-intervention (6 weeks after pre-intervention), and follow-up (18 weeks after pre-intervention).

#### Primary outcome

The primary outcome for this trial will be the sum score on the 30-item *Inventory of Depressive Symptomatology* (*IDS*) [56] at post-intervention. The IDS is a well-established measure of depressive symptoms [57].

#### Secondary outcomes

Secondary outcomes include post-intervention sum scores on the following measures: the *Generalized Anxiety Disorder Questionnaire-IV* (*GADQ-IV*) [58], a 10-item questionnaire assessing generalized anxiety symptoms; the 17-item *Social Phobia Inventory* (*SPIN*) [59] measuring social anxiety symptoms; the 22-item *Ruminative Response Scale* (*RRS*) [49], a well-established measure of depressive rumination; the *Penn State Worry Questionnaire* (*PSWQ*) [50], a 16-item scale assessing pathological worry; and the *Perseverative Thinking Questionnaire* (*PTQ*) [17], a validated 15-item questionnaire measuring process features of RNT such as repetitiveness and intrusiveness of thoughts regardless of typical thought content.

Further measures that will be administered at all three measurement timepoints are as follows: the 9-item *Patient Health Questionnaire-9* (*PHQ-9*) [51], a self-report measure for diagnosing major depression; the 7-item *Generalized Anxiety Disorder-7 Questionnaire* (*GAD-7*) [52], a self-report measure for generalized anxiety disorder; and the 20-item *Social Interaction Anxiety Scale* (*SIAS*) [53], a self-report questionnaire for diagnosing social anxiety disorder.

Demographic data and additional health-related data such as current psychotherapy and current medication will only be assessed at baseline (pre-intervention and randomization).

### Participant timeline {13}

Eligible participants will complete the pre-intervention assessment including measures for the primary outcome (depressive symptoms) and secondary outcomes (generalized anxiety symptoms, social anxiety symptoms, RNT) of the study. Consequently, participants will be randomly allocated to one of the three trial conditions. Participants in both active conditions (conditions (1) and (2)) will use the respective app for 6 weeks. Primary and secondary outcomes will be measured again at post-intervention (6 weeks after pre-intervention) and follow-up (18 weeks after pre-intervention). All participants will provide informed consent prior to data acquisition, randomization, and use of intervention apps. For an overview of the study procedure, see Figs. 1 and 2.

**Fig. 1 Fig1:**
[figure not shown]
Schedule of enrolment, interventions, and assessment

**Fig. 2 Fig2:**
[figure not shown]
CONSORT flow diagram

### Sample size {14}

We conducted a power analysis in G*Power [60] based on the minimal clinically important difference (MICD) in depressive symptoms (primary outcome). Measures of depressive symptoms have an established MCID of *d* = 0.48 [61], which also provided the basis for the power analysis in other recent trials testing app-based prevention [54]. Using this effect size, with 90% power and an alpha level of 0.05, the sample size required for a 2-arm two-sided comparison at post-intervention would be 93 participants per arm. To account for 20% expected dropout at post-intervention, a total sample size of 351 (117 per trial arm) will be needed to test whether the two app-based interventions (the full RNT-focused intervention and the concreteness training intervention) significantly reduce depressive symptoms relative to the waiting list control condition. The required sample size was calculated for a two-arm comparison (even though the study has three arms) as we do not have any a priori hypotheses regarding whether one of the apps will be more efficacious.

### Recruitment {15}

Participants will be recruited via advertisements on social media (e.g., on Facebook, Instagram, Twitter), mailing lists, and newsletters, as well as other circulars and noticeboards within willing schools and universities. School psychologists of willing schools will be contacted and provided with detailed information about the trial to support recruitment in single schools. As an incentive to participate, participants will have the opportunity to take part in a lottery after they completed the study. Alternative to this, participants studying psychology or a related subject at LMU Munich can receive partial course credit for completing the study.

## Assignment of interventions: allocation

### Sequence generation {16a}

Participants will be randomized (in a 1:1:1 ratio) to the three trial arms. Randomization will be conducted independently using pre-generated computerized allocations based on blocking with variable block sizes. As many of the study outcomes such as depressive symptoms and RNT are known to be distributed unequally across genders [62, 63], randomization will be stratified according to gender (male, female, non-binary).

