### Concealment mechanism {16b}

Randomization will be conducted in REDCap based on a pre-generated randomization table applying block randomization and stratification by gender. Allocation concealment will be ensured, as the allocation code will not be visible for the study team before a participant has been assigned to one of the treatment conditions.

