## Statistical methods

### Statistical methods for primary and secondary outcomes {20a}

#### Primary analyses

A linear mixed-effects model will be computed to analyze whether the two versions of the app reduced depressive symptoms (sum score on the IDS, primary outcome variable) relative to the control condition. In the model, the effect of condition (full RNT-focused intervention, concreteness training intervention, waiting list control condition), time (pre-intervention, post-intervention), and condition × time interaction will be tested. Simple slope tests will be conducted to determine whether (a) the full RNT-focused intervention significantly reduced depressive symptoms relative two the waiting list control condition and (b) the concreteness training intervention significantly reduced depressive symptoms compared to the waiting list control condition.

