#### Secondary analyses

The primary analyses will be repeated for the secondary outcomes depressive rumination (RRS sum score), worry (PSWQ sum score) content-independent RNT (PTQ sum score), generalized anxiety symptoms (GADQ-IV sum score), and social anxiety symptoms (SPIN sum score), respectively. *P-*values will be adjusted using Holm’s procedure [74] to reduce the chance of finding false positives due to multiple outcome variables.

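### Randomization is stratified by gender because outcomes differ by gender, but the stated models do not name gender; the effect is small and conservative, and the remedy is cheap

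*Protocol article*

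**What the plan says.** **Design.** Under Sequence generation {16a} the protocol article states: "randomization will be stratified according to gender (male, female, non-binary"). It gives the reason in the same sentence: "As many of the study outcomes such as depressive symptoms and RNT are known to be distributed unequally across genders". Concealment mechanism {16b} confirms the method, a "pre-generated randomization table applying block randomization and stratification by gender". Allocation is 1:1:1.

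**Analysis.** Under Primary analyses {20a} a linear mixed-effects model of the IDS sum score is to test "the effect of condition (full RNT-focused intervention, concreteness training intervention, waiting list control condition), time (pre-intervention, post-intervention") and the condition × time interaction, followed by simple slope tests of each app against the waiting list. Under Secondary analyses, "The primary analyses will be repeated for the secondary outcomes": RRS, PSWQ, PTQ, GADQ-IV and SPIN. The exploratory logistic regressions on probable diagnoses list no covariates. The missing-data section {20c} names full information maximum likelihood (FIML) and intention to treat. None of these sections mentions gender.

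**Deferred.** Interim analyses {21b} promises a full SAP before the analysis and mentions interim, subgroup and sensitivity analyses. The section on additional analyses {20b} refers to the same plan. Neither lists the terms of the primary model among the deferred matters.

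**The concern.** The design treats gender as prognostic and the stated analysis does not mention it. Blocking within gender strata keeps the arms close to balanced on gender, so gender contributes little to the true variability of the arm difference. A model without gender still counts the gender variance as residual error. Its standard error is then somewhat larger than the true sampling error, the test is slightly conservative and some power is lost.

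What is at stake is a little precision, and the prespecification of the model. If the choice between an adjusted and an unadjusted analysis stays open until the data are in, it can be made on the results.

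**Working it through.** **Inputs from the protocol article, Sample size {14}:** d = 0.48, two-sided alpha 0.05, power 90%, 93 per arm evaluable, 20% dropout, 117 per arm, 351 in total.

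**Inputs that are assumed**, because the document gives none: the share of outcome variance explained by gender (R²), the pre-post correlation (0.5), the gender mix (20/77/3%) and the size of any gender × time effect.

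**Step 1. The plan's own figure.** The two-sample t-test needs 92.18, rounded up to 93 per arm (power 90.25% at 93). 93/0.8 = 116.25, rounded up to 117, and 3 × 117 = 351. The plan's figure is reproduced, and gender does not enter it.

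**Step 2. Comparison at post-intervention only.** This is how the trial was sized. Use the normal approximation with total SD 1:

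- ncp = 0.48/√(2/93) = 3.273.
- Under stratified allocation the true standard error is √(1−R²) times the one the unadjusted test uses.
- Type I error, unadjusted = 2 × [1 − Φ(1.96/√(1−R²))].
- Power, unadjusted = 1 − Φ((1.96 − ncp)/√(1−R²)).
- Power, adjusted = 1 − Φ(1.96 − ncp/√(1−R²)).

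| Assumed R² | √(1−R²) | Type I error, unadjusted | Power, unadjusted | Power, adjusted | Gain (points) |
|---|---|---|---|---|---|
| 2% | 0.990 | 4.8% | 90.8% | 91.1% | 0.3 |
| 5% | 0.975 | 4.4% | 91.1% | 91.9% | 0.8 |
| 8% | 0.959 | 4.1% | 91.5% | 92.7% | 1.2 |

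For R² = 8%: 1.96/0.959 = 2.043, giving 4.1%; (1.96 − 3.273)/0.959 = −1.369, giving 91.5%; 1.96 − 3.273/0.959 = −1.453, giving 92.7%.

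**Step 3. The contrast actually specified.** The treatment effect is carried by condition × time over two time points. With complete data its estimate is the difference between arms in mean pre-post change. If gender shifts the pre and post scores equally, the shift drops out of each participant's change, so a gender main effect alone can do nothing. Mixed models were fitted to 12 simulated data sets with gender-stratified permuted blocks, 117 per arm and a gender main effect of SD 0.3:

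- Complete data: adding the main effect left the estimate identical to rounding error, and the standard error changed by at most 0.002%.
- 20% dropout: the standard error changed by at most 0.6%, and the estimate moved by at most 0.021 SD.

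**Step 4. When gender also affects change.** The change score (SD 1 before any gender × time effect) was simulated with 20% dropout and 4,000 runs per setting. Monte Carlo error is about 0.3 points for type I error and 0.5 for power. The adjusted analysis enters gender as a covariate for change, which is what gender × time does in the mixed model.

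| Assumed gender × time SD | Type I error, without / with gender | Power, without / with gender |
|---|---|---|
| 0 | 5.2% / 5.2% | 90.0% / 90.0% |
| 0.1 | 5.1% / 5.2% | 90.2% / 90.2% |
| 0.2 | 4.9% / 5.1% | 89.3% / 90.4% |

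A closed-form check agrees. At SD 0.2 the unadjusted test uses a standard error √1.04 = 1.020 times the true one. Its power is Φ(3.273 − 1.96 × 1.020) = Φ(1.274) = 89.9%, against Φ(3.273 − 1.96) = 90.5% with adjustment. The gain is 0.7 points before rounding, of the same order as the simulated 1.1.

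**The case against.** Three arguments carry weight.

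1. **Silence is not exclusion.** The Primary analyses section lists effects to be tested. An adjustment covariate need not be a tested effect, the article is condensed, and a detailed SAP is promised. A reader might infer that the analysis ignores its own stratification; the document does not support that, because nothing in it says gender will be left out. What stands is narrower: the article sets out the model's terms, the sections that defer work to the SAP do not list those terms, and the published model does not use the variable the design treats as prognostic.

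2. **The post-only figures belong to a different analysis.** This is right for the mixed model as written. The post-only frame is still relevant: the primary outcome is defined as the IDS score at post-intervention, the trial was sized for a comparison at that time, and the logistic regressions are framed on status at post-intervention or follow-up. The reason given for stratifying concerns the level of the outcomes, though, and says nothing of change. The document offers no evidence of a gender × time effect.

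3. **The remedy is not quite free.** With three gender categories, gender plus gender × time adds 2 + 2 = 4 parameters, some resting on what may be a very small non-binary group. This stands, and a pooling rule is needed.

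A reader might also infer that FIML is compromised without gender. That would require gender to predict both dropout and the post score beyond the pre score and condition. The document does not suggest that dropout differs by gender, so this is at most a side benefit of inclusion.

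**Conclusion.** The point holds as a minor improvement. Gender is a stratification factor chosen because it is prognostic, and the models set out for the primary and secondary outcomes do not name it. In a post-only comparison the cost is about 0.3 to 1.2 points of power at an assumed R² of 2% to 8%, with type I error slightly below nominal. In the specified pre/post contrast the cost is nil if the gender effect is constant over time, and about 1 point at an assumed gender × time SD of 0.2.

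A reader might conclude that the tests are invalid or the trial underpowered. Neither follows: any departure from 5% attributable to the omission is in the conservative direction, and the calculation behind 351 does not depend on gender adjustment. The direction of the effect follows from the design; its size rests wholly on assumed values.

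**What to change.** State in the SAP, before the condition variable is unmasked, that the randomization stratum enters the models:

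- **Primary and secondary outcomes:** add gender and gender × time to the mixed model. Alternatively, use an ANCOVA of the post score with the pre score, condition and gender. A gender main effect alone is not enough in the repeated-measures form, because it cancels.
- **Logistic regressions on probable diagnoses:** consider gender as a covariate. Say whether the reported odds ratio is conditional on gender, because the adjusted and unadjusted odds ratios are different quantities.
- **Sparse stratum:** fix a rule for pooling the non-binary group, with the condition under which it applies, before unmasking.

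The cost is four extra parameters in the mixed model (two in the ANCOVA) and one pooling rule. The variable is already recorded at randomization, so neither data collection nor the sample size changes.

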### Concealment mechanism {16b}

Randomization will be conducted in REDCap based on a pre-generated randomization table applying block randomization and stratification by gender. Allocation concealment will be ensured, as the allocation code will not be visible for the study team before a participant has been assigned to one of the treatment conditions.

### Implementation {16c}

The randomization table providing the basis for the computerized allocation in REDCap will be created by an independent statistician outside the study team. Enrolment and the generation of the allocation code will be automatized via REDCap and hence cannot be influenced by the study team monitoring data collection.

## Assignment of interventions: blinding

### Who will be blinded {17a}

The analysis team will be blind to the trial condition. The variable condition will be masked by someone outside the analysis team before the analysis.

### Procedure for unblinding if needed {17b}

n/a, explanation: There is no blinding during data collection and thus no procedure for unblinding.

#### Data collection and management

### Plans for assessment and collection of outcomes {18a}

All assessments (pre-intervention, post-intervention, follow-up) will take place online. Data will be collected automatically via the survey platform REDCap. Only the following validated questionnaires will be used to measure the outcomes of this trial.

#### Questionnaires measuring RNT

Ruminative Response Scale (RRS): The RSS [49] (German version [64]) is a 22-item scale measuring the frequency with which respondents think about their depressive symptoms. Items such as “When I feel sad or down, I think about a past situation and wish it had gone better” are rated on a 5-point Likert scale ranging from “almost never” to “almost always”. The RRS has been shown to have good internal consistency, test–retest reliability, and high construct validity [65].

Penn State Worry Questionnaire (PSWQ): The PSWQ [50] (German Version [66]) is a 16-item questionnaire assessing the frequency, intensity, and uncontrollability of worry. Respondents are asked to rate the items such as “Many situations make me worry” on a 5-point Likert scale ranging from “not typical at all of me” to “very typical of me”. The PSWQ demonstrated high internal consistency as well as good convergent and discriminative validity [50].

Perseverative Thinking Questionnaire (PTQ): The PTQ [17] (which will be used in a German translation by the authors of the questionnaire) is a 15-item questionnaire assessing an individual’s general tendency towards repetitive negative thinking. Unlike the PSWQ and the RRS, the PTQ measures process features of RNT rather than specific thought contents of RNT. Items such as “Thoughts intrude into my mind” are rated on a 5-point Likert scale ranging from “never” to “almost always”. The PTQ demonstrated excellent internal consistency as well as high construct validity [17].

#### Questionnaires measuring depressive and anxiety symptoms

Inventory of Depressive Symptomatology (IDS): The IDS [56] is a 30-item questionnaire measuring depressive symptoms. For the current trial, a German translation of the IDS [67] will be used. Participants are asked to read statements about different depressive symptoms (e.g., “feeling sad”) and chose one of four statements (e.g., “I do not feel sad”, “I feel sad less than half the time”, “I feel sad more than half the time”, “I feel sad nearly all of the time”), which describe their state during the past 7 days most accurately. The IDS demonstrated excellent internal consistency in sub-clinical sample with Cronbach’s *α* ranging between 0.92 and 0.94 and good internal consistency in samples with current depression with Cronbach’s α ranging between 0.76 and 0.82 [56]. High correlations between the IDS and other measures of depressive symptoms indicate good construct validity [56].

Social Phobia Inventory (SPIN): The SPIN [59] (which will be used in a German translation [68]) is a 17-item measure of social anxiety symptoms. Participants are asked to rate items like “I am bothered by blushing in front of people” on a 5-point Likert scale ranging from “not at all” to “extremely”. The SPIN was shown to have good internal consistency, test–retest reliability, and high construct validity [59].

Generalized Anxiety Disorder Questionnaire-IV (GADQ-IV): The GADQ-IV [58] (which will be administered in a German translation [69]) is a 10-item scale assessing the presence and intensity of generalized anxiety disorder symptoms, such as the excessiveness and uncontrollability of worry and related physical symptoms. The answer formats are dichotomous yes–no questions for detecting the presence/absence of different symptoms and 9-point Likert scales ranging from “none” to “very severe” to assess functional impairment and subjective distress through symptoms. The GADQ-IV demonstrated high test–retest reliability as well as good convergent and discriminant validity [58].

#### Self-report questionnaire measures of probable psychiatric diagnoses

Patient Health Questionnaire-9 (PHQ-9): The PHQ-9 [51] (German version [70]) is a 9-item questionnaire commonly used for screening for depression. Respondents are asked to rate how much they have been bothered by problems such as “little interest or pleasure in doing things” on a 4-point Likert scale ranging from “not at all” to “nearly every day”. The PHQ-9 was shown to have good psychometric properties and there is high agreement between PHQ diagnoses of depression and those of independent mental health professionals [51].

##### Generalized Anxiety Disorder-7 Questionnaire (GAD-7)

The GAD-7 [52] (German version [71]) is a 7-item questionnaire commonly used for screening for generalized anxiety disorder. Participants are asked to rate how much they have been bothered by problems such as “Feeling afraid as if something awful might happen” on a 4-point Likert scale ranging from “not at all” to “nearly every day”. The GAD-7 was found to have good psychometric properties and validity as a screener for generalized anxiety disorder [52].

Social Interaction Anxiety Scale (SIAS): The SIAS [53] (German version [72]) is a 20-item scale assessing anxiety in social interaction and being observed by others. Respondents are asked to rate items such as “I get nervous if I have to speak with someone in authority (teacher, boss, etc.)” on a 5-point Likert scale ranging from “not at all” to “extremely”. The SIAS was shown to have good psychometric properties [53] and to be a valid screener for social anxiety disorder [73].

### Plans to promote participant retention and complete follow-up {18b}

To promote participant retention, participants can only receive reimbursement for their participation (either partial course credit or taking part in the lottery and having the opportunity to win an Amazon voucher) when they completed all three assessments of the study (pre-intervention, post-intervention, follow-up). To promote retention in the control group, the trial has a waiting list control condition, in which participants can download one of the two intervention apps after they completed the study.

### Data management {19}

Primary data will be collected via the software REDCap, which is running on secure, encrypted faculty servers of the LMU Munich. Metadata about the app use (frequency, which different parts of the app have been used) will be collected via the software m-Path. Pseudonymized data will be extracted to a secure, encrypted internal study drive. As data will be collected automatically via online platforms specifically designed for research purposes, high data quality will generally be guaranteed. Data will be collected and stored in a pseudonymized manner whenever possible (for the management of personal data see item 27—confidentiality).

